
### Sample Size Estimate

The target number of participants was 30 (15 per group) based on feasibility. The detection power was calculated when the primary outcome (proportion of subjects with new or enlarged existing lesions detected on T2-weighted images) was compared using the Fisher exact test. With 60% of patients placed in the placebo group based on the results of the domestic phase II study (D1201 study) at the time of fingolimod development [16] and assuming a 5% proportion in the OCH group, the detection power was 86.5%. Furthermore, when the OCH group was set to 10%, the detection power was 74.6% (the significance level was set to 5% using a two-tailed test).

### Patient Clinicodemographic Characteristics

The following clinicodemographic information was recorded for each participant: (1) subject background (eg, birth date, sex, body height, body weight); (2) urine pregnancy test; (3) infectious disease or antibody test; (4) vital signs (blood pressure, pulse rate, body temperature, and breathing rate); (5) neurological symptoms rating scale (Expanded Disability Status Scale [EDSS] or functional disability scale); (6) clinical tests (hematological test, hematobiochemical test, or urine test); (7) 12-lead electrocardiogram; (8) echocardiography; (9) chest or abdominal X-ray; (10) abdominal computed tomography; (11) MRI; (12) peripheral blood gene expression level (reverse transcription–polymerase chain reaction); (13) frequencies of NK, NKT, T cells, or other lymphocyte subsets; (14) frequencies of Th1, Th2, or Th17 cells; (15) intestinal and oral microbiome; (16) adverse events; (17) combination drugs and important nondrug therapies; and (18) Columbia Suicide Severity Rating Scale.

### Outcome Measurements and Study Timeline

The outcomes that will be measured repeatedly throughout the trial and the corresponding time points are shown in Multimedia Appendix 1. The main outcome is MRI changes (the percentage of subjects with new or newly expanded lesions on T2-weighted MRI). In addition, the annual relapse rate, cumulative number of new or newly expanded lesions on T2-weighted MRI, percentage of subjects who did not have lesions at 12 and 24 weeks on T2-weighted images of head MRI compared to those at the preobservation period at 24 weeks, brain atrophy in T1-3D images, percentage of subjects with no contrast-enhanced lesions on gadolinium-enhanced T1-weighted images, number of contrast-enhanced lesions on gadolinium-enhanced T1-weighted images, changes in volume of demyelinating lesions on fluid-attenuated inversion recovery 3D images, diffusion tensor imaging changes in myelin sheath lesions, and changes in myelin sheath lesions by a myelin map will be assessed. Additional outcomes include the relapse-free period (from randomization to earliest relapse), sustained reduction in disability occurrence rate, period until sustained reduction in disability (from randomization), no evidence of disease activity, and exploratory biomarkers from phase I trials (peripheral blood gene expression, frequencies of lymphocyte subsets, and intestinal and oral microbiome) [13].

### Adverse Events

Adverse events, defined as any undesired or unintended sign (including abnormal fluctuations in each test value), symptoms, or illness that occurs between the start of investigational drug administration and end or discontinuation of the investigational drug (regardless of its association with the study drug), will be recorded. The recordings will include the degree of symptoms on a 1-5 scale (1=asymptomatic or mild adverse events, 5=death due to the adverse event), outcomes from 1 to 6 (1=event disappeared or normalized, 6=death), and association with the investigational drug from 1 to 4 (1=associated, 4=not associated).

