### Discontinuation Criteria

Discontinuation of involvement in the clinical trial may occur for any patient because of voluntary withdrawal or for any of the following reasons: (1) serious adverse events; (2) pregnancy; (3) alanine aminotransferase and aspartate aminotransferase >5-fold higher than the standard value upper limit; (4) total bilirubin exceeding 2.0 mg/dL; (5) number of peripheral blood lymphocytes <500/mm^3^ and administration of the investigational drug is stopped three times in a row without recovery, even after three tests; (6) occurrence of a grade-3 event based on Common Terminology Criteria for Adverse Events v4.0-JCOG; (7) new neurological symptoms with unpredictable MRI findings observed from the course of MS; (8) more than one recurrence of MS; (9) at least three courses of pulse steroid therapy performed; (10) an important management problem is discovered (subject noncompliance); (11) significant deviation from the protocol; (12) administration of the investigational drug is stopped at least three times, regardless of the reason; and (13) at the discretion of the principal investigator. If discontinuation occurs because of this final criterion, justification will be provided in the results report.

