### Administration of Trial Compound

The investigational drug OCH (3.0 mg) in the form of granules (total of 0.3 g) or placebo granules alone (0.3 g) was orally administered with approximately 150 mL of water 30 min before breakfast once weekly for the 24-week trial duration. The white granules were composed of crystalline cellulose, mannitol, sodium croscarmellose, low-substituted hydroxypropyl cellulose, and polysorbate 80.

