### Statistical Methods

Patient clinicopathological data will be summarized using descriptive statistics for each group. The proportion of subjects with new or enlarged existing lesions on T2-weighted MRIs in each group will be calculated and compared using the Fisher exact test with 95% CIs. The proportion of data between groups related to the primary endpoint will also be compared using the Fisher exact test with 95% CIs. For time-to-event data such as relapse-free periods, Kaplan-Meier estimates will be calculated for each group and groups will be compared using the log-rank test. The expression rates of safety-related outcomes and adverse events will be calculated for each group. For various test values, a list of measured values will be created for each group. The summary statistics for each group and measurement time point will also be calculated.

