## Discussion

### Principal Results

This will be the first randomized double-blind placebo-controlled trial to study the efficacy and safety of OCH. This randomized controlled trial will determine whether OCH is effective and safe in patients with MS. The results of this trial are expected to provide evidence for the potential of using OCH as a therapeutic agent for MS.

A single-dose trial (STEP 1) trial was conducted in healthy adults from November 2012 to July 2013 and a repeated-dose trial (STEP 2) was conducted in patients with RRMS from March 2014 to August 2017 [13]. In a phase I trial consisting of STEP 1 and STEP 2, OCH was administered to 28 patients (STEP 1: 3 patients×5 groups in all cohorts, STEP 2: 7 patients×1 group in a cohort, 3 patients×2 groups in a cohort).

Grade-1 adverse events and side effects were noted in STEP 1 and there were no serious adverse events or discontinuations. In STEP 2, serious side effects (acidosis and altered state of consciousness, depression, muscle weakness, and malaise) were reported in three patients in the 0.3 and 3 mg groups. Two patients discontinued treatment; however, all patients recovered. No other serious events were observed, confirming that the patients tolerated doses of 0.3, 1, and 3 mg. After OCH administration, there was no significant change in the neurological symptom evaluation scale score (EDSS or functional disability scale) even in STEP 2 because of the short observation period. MRI revealed clinically significant abnormalities in one patient in the 0.3 mg group; this patient discontinued the study.

A phase I physician-led clinical trial, conducted as an early exploratory clinical trial, determined that the dose was likely to have pharmacological action (fluctuations in some biomarkers) in humans. The dose at which pharmacological action was observed in experimental autoimmune encephalomyelitis model mice was 0.4-0.5 mg/kg. Considering that the area under the curve (AUC)_0-∞_ following oral administration of 5 mg/kg to mice was 2922 ng·h/mL, the AUC_0-∞_ following oral administration of 0.5 mg/kg (dose at which pharmacological action was observed) was estimated as 292.2 ng･h/mL. Assuming a correlation between systemic exposure (AUC_0-∞_) and pharmacological effects and systemic exposure in monkeys (AUC_0-∞_ after oral administration of 10 mg/kg was 2376, SD 1164 ng), pharmacological action may be expected in humans if at least approximately 1.2 mg/kg is orally administered.

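### Adverse event recording closes when study drug ends or is stopped, so later-onset events fall outside the definition and observation time can differ between arms in either direction

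*Protocol article*

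**What the plan says.** In the protocol article, Adverse Events, a recordable event is an undesired sign, symptom or illness, including abnormal test values, "that occurs between the start of investigational drug administration and end or discontinuation of the investigational drug", whether or not it is thought to be drug-related. Severity, outcome and relation to drug are graded for each event.

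Administration of Trial Compound gives the dosing as "once weekly for the 24-week trial duration".

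Discontinuation Criteria opens with "Discontinuation of involvement in the clinical trial may occur for any patient because of voluntary withdrawal or for any of the following reasons". The list includes safety triggers such as serious adverse events, liver values, lymphocyte counts and "occurrence of a grade-3 event based on Common Terminology Criteria for Adverse Events". It also includes disease-activity triggers: "more than one recurrence of MS" and repeated pulse steroid courses.

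For the analysis, Statistical Methods says "The expression rates of safety-related outcomes and adverse events will be calculated for each group". The article describes no recording period after treatment and no continued recording after an early stop.

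**The concern.** Safety stands beside efficacy in the trial's stated objective. The window is tied to each patient's own time on drug rather than to a common calendar, and this has two consequences.

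- **Lost events.** Anything with onset after the last dose, including within that final weekly interval, falls outside the definition. So does anything that starts after an early stop. The wording of the definition causes this, so an analysis plan cannot repair it.
- **Unequal observation.** A patient who stops at week *w* is observed for *w* weeks instead of 24. If stops differ in number or timing between arms, the group rates compare unequal lengths of follow-up.

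With "The target number of participants was 30 (15 per group) based on feasibility", a few unrecorded events can change how the safety comparison reads.

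**Working it through.** The plan gives no figure for observation time, early stops or expected adverse event rates, so there is nothing of its own to reproduce here. Its power figures do not bear on this point. The check has two parts.

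**1. The text side by side.** Adverse Events closes the window at end or discontinuation of drug. Discontinuation Criteria describes leaving the trial, not only stopping the drug, so it restores no follow-up. Statistical Methods takes rates by group from whatever was recorded. Recording time after drug is therefore 0 weeks for every patient, and a stop at week *w* removes 24 − *w* weeks.

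**2. How much this could matter.** Inputs from the documents are 15 patients per arm and 24 weeks. The number and timing of stops, the true event risk and a constant hazard are assumptions. Stops are taken as independent of events.

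Observation time with *k* stops at week *w* is (15 − *k*) × 24 + *k* × *w*.

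- No stops: 15 × 24 = 360 patient-weeks.
- 3 stops at week 12: 12 × 24 + 3 × 12 = 324. 1 stop at week 12: 14 × 24 + 12 = 348. Ratio 324/348 = 0.93.
- 5 stops at week 8: 10 × 24 + 5 × 8 = 280. 1 stop at week 8: 14 × 24 + 8 = 344. Ratio 280/344 = 0.81.
- 3 stops in each arm at the same week: ratio 1.00.

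The expected recorded proportion, with the same true risk *r* by week 24 in both arms, is [(15 − *k*) × *r* + *k* × (1 − (1 − *r*)^(*w*/24))] / 15.

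For *r* = 30%, the risk by week 12 is 1 − 0.7^(1/2) = 16.3%, and by week 8 it is 1 − 0.7^(1/3) = 11.2%.

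- 3 stops at week 12: (12 × 0.30 + 3 × 0.163)/15 = 27.3%. 1 stop: (14 × 0.30 + 0.163)/15 = 29.1%. Gap 1.8 points.
- 5 stops at week 8: (10 × 0.30 + 5 × 0.112)/15 = 23.7%. 1 stop: (14 × 0.30 + 0.112)/15 = 28.7%. Gap 5.0 points.

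Range over the assumed risk:

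| True risk by week 24 | 3 vs 1 stops, week 12 | 5 vs 1 stops, week 8 |
|---|---|---|
| 20% | 18.1% vs 19.4% | 15.7% vs 19.1% |
| 30% | 27.3% vs 29.1% | 23.7% vs 28.7% |
| 50% | 45.9% vs 48.6% | 40.2% vs 48.0% |

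At 30% the gaps amount to 0.018 × 15 ≈ 0.3 and 0.050 × 15 ≈ 0.75 of a patient. The arithmetic is symmetric: whichever arm has more stops shows the lower recorded proportion.

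**The case against.** A reader might infer that the window biases the comparison in favour of OCH, because toxicity would shorten OCH follow-up. The documents do not support this. Relapse and repeated pulse steroids are also stopping criteria. If OCH works, those stops would fall more on placebo and shorten placebo follow-up instead. In addition, an event that triggers a stop began on drug, so it is recorded and graded. Only events with later onset are lost. The illustration does not model stops caused by events, so it does not measure that scenario.

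A reader might also take the phase I repeated-dose step as a forecast. Principal Results reports "Two patients discontinued treatment; however, all patients recovered", out of 7 + 3 + 3 = 13 patients. That count pools three dose levels, comes with no placebo stop rate, and does not make clear how many stops were for toxicity. It shows that early stops can happen, not that they will differ between arms.

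The requirement for contraception until 90 days after the last dose is a reproductive precaution. It does not establish a 90-day risk period for adverse events in general, and the documents give no human half-life.

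Exposure-adjusted rates may properly be left to the analysis plan, so their absence here is no fault. The end of the drug might be read as the end of the 24-week treatment period, which would cover a completer's last dosing interval. The text does not say so, and that reading does nothing for patients who stop early. The visit schedule (Multimedia Appendix 1) is not shown. If it holds a later safety visit, that visit and the definition would need reconciling.

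All of these objections stand. None of them supplies recording after the last dose or after an early stop.

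**Conclusion.** The point holds in limited form. As written, the definition excludes every event with onset after the drug ends or is stopped, and it lets observation time differ between arms. The first part follows from the wording alone. The second depends on stops being unequal, and its direction is unknown.

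Under the assumed stop patterns the observation-time ratio is 0.81 to 0.93. At an equal true risk of 30%, the gap in recorded proportions is about 2 to 5 points, or under one patient in 15. Over risks of 20% to 50% it runs from about 1 to 8 points. These are illustrations, not forecasts. The documents support neither a bias towards OCH, nor an expected difference in stopping, nor a 90-day recording period.

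**What to change.** Define the adverse event window for every treated patient as first dose to the later of the planned week-24 assessment and at least one dosing interval after the last dose. Apply it regardless of early stopping and as far as the patient's consent allows. The stopping criteria themselves need not change. Say explicitly that leaving treatment does not end safety recording for patients who still agree to contact. Report the number and timing of early stops and the observation time by arm beside the adverse event rates.

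Under this window a patient who stops at week 8 contributes 24 weeks instead of 8, and each arm reaches at least 360 patient-weeks if all patients agree.

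The cost is modest extra contact with patients who stopped and somewhat more events recorded. The article's Results section states that enrolment closed in June 2021 and analysis was completed in March 2023, so collection in this trial can no longer change. Here the report should state the window actually used, give stops and observation time by arm, and disclose any later events that are known. The new definition belongs in any successor protocol.

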### Discontinuation Criteria

Discontinuation of involvement in the clinical trial may occur for any patient because of voluntary withdrawal or for any of the following reasons: (1) serious adverse events; (2) pregnancy; (3) alanine aminotransferase and aspartate aminotransferase >5-fold higher than the standard value upper limit; (4) total bilirubin exceeding 2.0 mg/dL; (5) number of peripheral blood lymphocytes <500/mm^3^ and administration of the investigational drug is stopped three times in a row without recovery, even after three tests; (6) occurrence of a grade-3 event based on Common Terminology Criteria for Adverse Events v4.0-JCOG; (7) new neurological symptoms with unpredictable MRI findings observed from the course of MS; (8) more than one recurrence of MS; (9) at least three courses of pulse steroid therapy performed; (10) an important management problem is discovered (subject noncompliance); (11) significant deviation from the protocol; (12) administration of the investigational drug is stopped at least three times, regardless of the reason; and (13) at the discretion of the principal investigator. If discontinuation occurs because of this final criterion, justification will be provided in the results report.

### Administration of Trial Compound

The investigational drug OCH (3.0 mg) in the form of granules (total of 0.3 g) or placebo granules alone (0.3 g) was orally administered with approximately 150 mL of water 30 min before breakfast once weekly for the 24-week trial duration. The white granules were composed of crystalline cellulose, mannitol, sodium croscarmellose, low-substituted hydroxypropyl cellulose, and polysorbate 80.

### Statistical Methods

Patient clinicopathological data will be summarized using descriptive statistics for each group. The proportion of subjects with new or enlarged existing lesions on T2-weighted MRIs in each group will be calculated and compared using the Fisher exact test with 95% CIs. The proportion of data between groups related to the primary endpoint will also be compared using the Fisher exact test with 95% CIs. For time-to-event data such as relapse-free periods, Kaplan-Meier estimates will be calculated for each group and groups will be compared using the log-rank test. The expression rates of safety-related outcomes and adverse events will be calculated for each group. For various test values, a list of measured values will be created for each group. The summary statistics for each group and measurement time point will also be calculated.

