**Methods:**

This protocol describes a double-blind, multicenter, placebo-controlled, randomized phase II clinical trial that was initiated in September 2019. The participants were randomly assigned to either a placebo control group or an OCH-NCNP1 group and the investigational drug (3.0 mg) was orally administered once weekly for the 24-week duration. Major inclusion criteria are as follows: patients had been diagnosed with relapsing MS (relapsing-remitting and/or secondary progressive MS) based on the revised McDonald criteria or were diagnosed with MS by an attending physician as noted in their medical records; patients with at least two medically confirmed clinical exacerbations within 24 months prior to consent or one exacerbation within 12 months prior to consent; patients with at least one lesion suspected to be MS on screening magnetic resonance imaging (MRI); and patients with 7 points or less in the Expanded Disability Status Scale during screening. Major exclusion criteria are as follows: diagnosis of neuromyelitis optica and one of optic neuritis, acute myelitis, and satisfying at least two of the following three items: (1) spinal cord MRI lesion extending across at least three vertebral bodies, (2) no brain MRI lesions during onset (at least four cerebral white matter lesions or three lesions, one of which is around the lateral ventricle), and (3) neuromyelitis optica–immunoglobulin G or antiaquaporin-4 antibody-positive. Outcome measures include the primary outcome of MRI changes (the percentage of subjects with new or newly expanded lesions at 24 weeks on T2-weighted MRI) and the secondary outcomes annual relapse rate (number of recurrences per year), relapse-free period (time to recurrence), sustained reduction in disability (SRD) occurrence rate, period until SRD (time to SRD occurrence), no evidence of disease activity, and exploratory biomarkers from phase I trials (such as gene expression, cell frequency, and intestinal and oral microbiome).

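### The primary Fisher test is valid but uses no baseline covariate; adjusting for one already-collected MRI measure would add an estimated 2 to 10 points of power, depending on an undocumented correlation

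*Protocol article*

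**What the plan says.** Under Statistical Methods, the primary proportion is handled by Fisher's test: "The proportion of subjects with new or enlarged existing lesions on T2-weighted MRIs in each group will be calculated and compared using the Fisher exact". Confidence intervals at the 95% level are to accompany it. No covariate or stratum is named. The Sample Size Estimate rests on the same method: the primary outcome "was compared using the Fisher exact test", and "the significance level was set to 5% using a two-tailed test". Its inputs are:

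- Size: "The target number of participants was 30 (15 per group) based on feasibility".
- Placebo rate: "With 60% of patients placed in the placebo group based on the results of the domestic phase II study (D1201 study").
- First OCH scenario: "assuming a 5% proportion in the OCH group, the detection power was 86.5"%.
- Second OCH scenario: an OCH rate of 10%, with a stated power of 74.6%.

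On baseline imaging, the abstract's Methods lists among the major inclusion criteria "patients with at least one lesion suspected to be MS on screening magnetic resonance imaging (MRI"), and Textbox 1 repeats it. Outcome Measurements and Study Timeline plans "changes in volume of demyelinating lesions on fluid-attenuated inversion recovery 3D images", which needs a baseline volume. The same section lists the number of contrast-enhanced lesions. Study Design describes random assignment and names no stratification factor.

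**The concern.** Entry is broad: relapsing-remitting or secondary progressive disease, EDSS up to 7, and one or more lesions. Patients are therefore likely to differ in their underlying tendency to form new lesions. In a crude 2x2 comparison that variation stays in the error.

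Chance imbalance also matters at this size. Suppose a factor is present in 15 of the 30 patients and allocation is unrestricted apart from 15:15. The groups then differ by only one patient with probability 2 × C(15,7) × C(15,8) / C(30,15) = 2 × 6435² / 155,117,520 = 0.53. In the other 47% of allocations they differ by at least 3 patients (20 percentage points), and an unadjusted comparison carries that difference into the estimate.

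At stake are power and ease of interpretation in a trial whose Limitations section names small sample size as its primary weakness. The data for a remedy appear to be collected already.

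**Working it through.** **1. The plan's own power figures.** The inputs are n = 15 per group, placebo 60%, OCH 5% or 10%, and two-sided alpha 5%. The Walters arcsine approximation to Fisher power is

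Φ( √(2n) × [asin√(p1 − 1/(2n)) − asin√(p2 + 1/(2n))] − 1.96 ).

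- OCH 5%: asin√0.5667 = 0.8523 and asin√0.0833 = 0.2928. The difference 0.5594 × √30 = 3.064, and Φ(3.064 − 1.96) = 86.5%.
- OCH 10%: asin√0.1333 = 0.3738. The difference 0.4785 × √30 = 2.621, and Φ(2.621 − 1.96) = 74.6%.

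Both stated figures reproduce. Exact enumeration of the Fisher test gives 88.6% and 73.9%.

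**2. A rough formula for adjustment.** Dividing the signal by √(1 − r²), where r is an assumed baseline–outcome correlation, gives:

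| r | OCH 5% | gain | OCH 10% | gain |
|---|---|---|---|---|
| 0.3 | 89.5% | 2.9 | 78.4% | 3.9 |
| 0.4 | 91.7% | 5.1 | 81.6% | 7.0 |
| 0.5 | 94.3% | 7.8 | 85.7% | 11.1 |

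This formula applies the same r to both groups, which is too generous when the OCH rate is low. With a normal covariate and a common log-odds slope of 1.5, r is 0.52 at a 60% event rate but 0.37 at 10% and 0.28 at 5%. At a 5% rate, the largest r possible with a normal covariate is 0.47.

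**3. Simulation that isolates the covariate.** The setting is 15:15, placebo 60%, a standard normal covariate, 4,000 trials per row and 1,999 re-randomizations. The adjusted test regresses the 0/1 outcome on the covariate, ignoring treatment, and re-randomizes the between-group difference in residuals. The comparator is an unadjusted exact test run at its full 5% size, so that Fisher's conservatism is not credited to the covariate.

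| log-odds slope (placebo r) | OCH 5%: unadjusted → adjusted | OCH 10%: unadjusted → adjusted |
|---|---|---|
| 0 (0) | 94.5 → 94.2 (−0.3) | 85.3 → 85.4 (+0.1) |
| 0.7 (0.31) | 94.3 → 96.0 (+1.7) | 84.2 → 87.8 (+3.6) |
| 1.0 (0.41) | 93.8 → 96.2 (+2.4) | 84.5 → 89.9 (+5.4) |
| 1.5 (0.52) | 94.4 → 98.2 (+3.8) | 84.0 → 92.1 (+8.1) |

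Other runs of the same test, with binary or continuous covariates, span a slightly wider range. At OCH 10% the gain was as low as 2 to 3 points at r about 0.3 and as high as about 10 points at r about 0.5. At OCH 5% it reached about 5 points. Simulated type I error was between 3.6% and about 5.5%, where values above 5% are within Monte Carlo error.

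**4. What belongs to Fisher's conservatism.** At 15 per group the actual size of the Fisher test is only about 1.6% to 1.7% for common rates of 20% to 60%. An unadjusted Boschloo test reaches 94.3% and 84.5%, which is 94.3 − 88.6 = 5.7 and 84.5 − 73.9 = 10.6 points above exact Fisher with no baseline value used. That gap is a separate matter and is not counted here.

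**The case against.** The strongest case for leaving the plan alone has five parts.

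- **Validity.** Fisher's test is valid, matches the power calculation and suits a feasibility-sized phase II trial with about 10 expected events (15 × 0.60 + 15 × 0.05 = 9.75, or 10.5 at an OCH rate of 10%). This stands: nothing is misstated.
- **Unknown prognostic strength.** No document gives r, and at 0.3 the gain is small. This stands, so the size can only be given as a conditional range.
- **Baseline is already used.** New or enlarged lesions are judged against an earlier scan. A reader might infer that the analysis ignores the pre-treatment MRI altogether. The document does not support that, because the earlier scan defines the outcome. What is absent is a baseline covariate in the comparison.
- **Unseen documents.** Stratification factors and supportive adjusted analyses may be in the full protocol or the SAP. A reader might infer from the article's silence that the design does nothing about imbalance, and that cannot be concluded. It does not remove the point, because the article states the method of the primary comparison and that method is unadjusted.
- **Timing.** The article's Results section reports a full analysis set of 30, analysis completed in March 2023 and a preliminary efficacy impression. A covariate chosen now would be post hoc. This stands and limits the remedy for this trial.

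Ordinary logistic adjustment would also be a poor substitute. The chance of no event on OCH is 0.95^15 = 46% at a 5% rate and 0.90^15 = 21% at 10%, and the adjusted likelihood-ratio test had a simulated size of about 6% to 7%. This objection does not reach a re-randomization test.

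**Conclusion.** The point holds as one of efficiency. The stated primary test is valid but leaves out a baseline covariate that appears to be available for every patient. Adjustment alone is worth roughly 2 to 5 points of power at an OCH rate of 5% and 2 to 10 points at 10%. It is worth practically nothing if the covariate is not prognostic.

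This range rests on an assumed placebo-group correlation of 0.3 to 0.5, a placebo rate of 60% and 15 per group. It also assumes a baseline effect on the log-odds scale that is common to both groups.

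Two stronger readings are tempting and should be resisted. A loss of 8 to 11 points follows only from setting r = 0.5 in both groups in the rough formula, which is close to or above what a 5% event rate allows. The full gap between the planned Fisher test and an adjusted re-randomization test is larger still, but much of it comes from Fisher's conservatism.

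**What to change.** Make the primary test a re-randomization test with one prespecified baseline covariate:

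1. Use log baseline FLAIR lesion volume. Use the baseline enhancing-lesion count only if a pre-treatment enhanced scan was taken in all patients; the article text does not confirm this, and its schedule appendix is not shown.
2. Regress the 0/1 outcome on the covariate, ignoring treatment, and take the between-group difference in residuals.
3. Obtain the two-sided p-value by re-randomizing labels under the allocation scheme actually used.
4. Report the covariate-standardized risk difference with a 95% CI, and keep the Fisher result as a sensitivity analysis.

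The cost is a change of wording in Statistical Methods and a short program, with no extra patients or scans. The covariate must be fixed before unblinding, and the gain is small if it is weakly prognostic. Since the analysis is reported complete, label the adjusted result as supplementary in this trial and adopt it as primary in a successor.
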